#### Analyses of primary endpoint

The primary endpoint of the randomized controlled trial, will be compared by t-test (if normally distributed) or by Mann-Whitney U test (if non-normally distributed) for statistical significance.

We will perform an intention-to-treat analysis including all randomized individuals having data on the outcome (primary or secondary). In addition, we will perform per-protocol analyses including all participants who took at least 80% of dosages.

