### Statistical approach

#### Sample size calculations

Based on the Natural History Study of FOP, progression of HO in FOP is estimated at 120,000 mm^3^ on average per 6-month period with a standard deviation of 48,000 mm^3^ [24]. Expert consensus defines a meaningful decrease in the rate of HO progression as at least 50% reduction in treated vs. control patients, or 60,000 mm3, with a standard deviation of 24,000 mm^3^. Using this projected impact, using a t-test with two-sided alternative, with unequal variances, a trial with treatment and placebo arms of *n* = 8 each would be 80% powered to detect this minimum clinically meaningful difference with an α = 0.05 during the initial 6-month study.

Taking into account an expected drop-out rate of 20%, we calculated the necessary number of participants to be 20 at the start of the study.

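### The primary test is chosen by a normality check on 8 to 10 patients per arm, so the hypothesis behind the primary p-value is not fixed in advance

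*Protocol article*

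**What the plan says.** Under Analyses of primary endpoint, the protocol article has the primary endpoint compared "by t-test (if normally distributed) or by Mann-Whitney U test (if non-normally distributed) for statistical significance". It names no default test. Under Analyses of secondary endpoints, the same rule is repeated for the change in whole-body NaF SUV.

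The Sample size calculations section works on the mean scale throughout. Control progression is "estimated at 120,000 mm^3^ on average per 6-month period with a standard deviation of 48,000 mm^3". The target is "at least 50% reduction in treated vs. control patients, or 60,000 mm3, with a standard deviation of 24,000 mm^3". The test is specified as "using a t-test with two-sided alternative, with unequal variances", and with it "treatment and placebo arms of *n* = 8 each would be 80% powered" "with an α = 0.05 during the initial 6-month study". The section then gives the total: "Taking into account an expected drop-out rate of 20%, we calculated the necessary number of participants to be 20".

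The Randomisation section keeps patients and the study team blinded until the analysis is finished. The Discussion describes marked heterogeneity in progression but gives no figure for it.

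**The concern.** The two branches answer different questions. The t-test addresses the difference in mean change in mm³, which is the scale on which the 50% target is defined. Mann-Whitney addresses whether values in one arm tend to rank above those in the other. If the data choose the branch, the null hypothesis behind the primary p-value is known only afterwards.

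The choice rests on 8 to 10 values per arm, where a normality check has little ability to tell a normal from a skewed distribution. In a trial this small the two tests will sometimes fall on opposite sides of 0.05. The primary verdict can then turn on the result of the check rather than on the treatment comparison.

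**Working it through.** **Inputs from Sample size calculations.** Control mean 120,000 and SD 48,000 mm³; treated mean 60,000 and SD 24,000 mm³; two-sided α 0.05; 8 evaluable per arm; 20 randomised, so 10 per arm before drop-out. The CV is 48/120 = 24/60 = 0.4 in both arms.

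**The plan's own figure (in thousand mm³).** SE = √(48²/8 + 24²/8) = √(288 + 72) = √360 = 18.97. Noncentrality = 60/18.97 = 3.16. Satterthwaite df = 360² / [(288² + 72²)/7] = 10.3. Power from the noncentral t is 81.5% (74.7% at 7 per arm), so 8 per arm for 80% power reproduces. With 20% drop-out, 16/0.8 = 20 also reproduces. At 10 per arm, SE = √(230.4 + 57.6) = 16.97, df = 13.2 and power is 90.5%.

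**Assumption about the check.** The article names none. Shapiro-Wilk at 5% in each arm is assumed, with Mann-Whitney used if either arm fails and Welch otherwise. For truly normal data the expected rate of misrouting is then 1 − 0.95² = 9.75%.

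**Simulation.** 4,000 trials per row, with exact Mann-Whitney. Monte Carlo SE is about 0.4 points for a rate near 6.5% and 0.6 points for a power near 80%.

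| Data | n per arm | Called non-normal | Welch power | Mann-Whitney power | Two-stage power | Tests disagree |
|---|---|---|---|---|---|---|
| Normal, plan's means and SDs | 8 | 10.6% | 80.3% | 79.7% | 80.6% | 6.5% |
| Same | 10 | 9.3% | 90.9% | 87.9% | 90.7% | 5.0% |
| Log-normal, plan's means and SDs | 8 | 24.3% | 88.2% | 90.6% | 90.7% | 5.1% |
| Same | 10 | 30.4% | 94.9% | 95.5% | 96.2% | 3.0% |
| Log-normal, CV 1 (assumed), means 120 and 60 | 8 | 63.3% | 20.1% | 32.7% | 31.7% | 15.6% |
| Same | 10 | 74.4% | 26.6% | 36.8% | 38.5% | 15.5% |

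Repeat runs gave disagreement of 6.7–7.3% (normal, 8 per arm), 5.3% (normal, 10 per arm), 4.9–5.6% (log-normal, 8 per arm), 2.8% (log-normal, 10 per arm) and, in one run, 13.7% (CV 1, 8 per arm).

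**Reading the table.**
- Reliability of the check: about 10% of normal data sets are sent to the rank test. Log-normal data at the plan's CV pass as normal in about 75% of trials at 8 per arm and 70% at 10 (1 − 0.243 and 1 − 0.304).
- Power on the plan's inputs: the rule costs nothing (80.6% against 80.3% at 8 per arm).
- Type I error under identical distributions: the two-stage rule rejects in 4.8% (8 per arm) and 5.5% (10 per arm) with normal data, and in 5.3% at both sizes with CV 1.

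**The case against.** The strongest reply is that the rule does little harm on the plan's own figures. That is correct: power is unchanged, type I error stays near 5%, and the 15% disagreement appears only with a CV of 1, which the article nowhere states. Blinding until the analysis is complete also limits deliberate choice of a test. It does not remove the dependence on the data.

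A second reply is that the normality criterion may stand in an analysis plan that is not shown. It may, and its absence is not the complaint. The article itself fixes a choice between two hypotheses by a distributional check, and no criterion makes such a check reliable at this size.

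Three stronger readings are tempting, and the article does not support them:
- **That the analysis reverts to a pooled-variance t-test.** The analysis section does not give the variance form. The only form named anywhere is the unequal-variance one. At 8 per arm the pooled SE is also the same: √(1,440 × 2/8) = √360, where 1,440 = (48² + 24²)/2.
- **That the Mann-Whitney branch would leave the trial unable to report mm³.** The rule selects a significance test and does not restrict which estimates are reported.
- **That the rule inflates false positives.** Rejection above 5% appears when means are equal but shapes differ. With log-normal CVs of 1 and 0.5 (assumed), the two-stage rule rejects in about 10% and Welch in 6–7%. Equal means with different shapes is not the absence of a drug effect, and the size depends wholly on the shapes assumed.

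**Conclusion.** The point holds as a moderate one. An unspecified check on 8 to 10 values per arm decides whether the primary p-value refers to the mm³ mean difference the trial was sized on or to rank ordering. The defect is a data-dependent hypothesis and, in some trials, a data-dependent verdict. It is not lost power or inflated error.

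The two candidate tests disagree at 0.05 in about 5–7% of trials under the plan's normal alternative, in 3–5% or slightly more with log-normal data at the same means and SDs, and in about 15% if the CV were 1. These figures assume Shapiro-Wilk per arm at 5%, equal arms, 24,000 mm³ as the treated-arm SD (the reading that reproduces the stated power), and log-normal shapes where skew is considered.

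**What to change.** Delete the normality condition under Analyses of primary endpoint and name one test before unblinding. Suggested wording: *The 6-month change in HO volume is compared between arms by a two-sided unequal-variance (Welch) t-test at the 5% level, and the difference in mean change in mm³ is reported with its 95% CI. A Mann-Whitney U test with the Hodges-Lehmann estimate is a sensitivity analysis and does not alter the primary conclusion.*

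Remove the same condition for NaF SUV under Analyses of secondary endpoints and name one test for each comparison. Comparison B sets the same patients against themselves, so it needs a within-patient test.

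The cost is a few sentences and no patients: Welch power on the plan's inputs is about 81% at 8 per arm and 90% at 10. The real downside is skew. If the CV were 1 (assumed), Welch would have about 10–13 points less power than the rank test (about 20% against 33% at 8 per arm). Naming any single test in advance would cure the data dependence; Welch is preferred because it matches the sizing and the mm³ target. Baseline or site adjustment and a re-randomisation p-value within site blocks are optional refinements.

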#### Analyses of secondary endpoints

To analyse the secondary endpoints of radiographic HO progression across all time points in comparison groups B and C, we will use linear mixed models for statistical significance.

Changes in whole body ^18^F NaF SUV will be measured in comparison groups A and B and compared by t-test (if normally distributed) or by Mann-Whitney U test (if non-normally distributed) for statistical significance.

Changes in CAJIS, SF-36 Quality of Life, range of motion surveys and the FOP Independent Activity of Daily Living (FOP I-ADL) will be compared in comparison groups A and B by linear mixed models. The impact of treatment on total joint mobility (measured as positive and negative changes in degrees of range of movement (ROM) for each axis), and changes in the mobility of specific subsets of joints, will be tested in comparison groups A and B via linear mixed models wherever possible.

The correlation between changes in joint ROM and radiographic progression of HO by whole body CT will be tested by Spearman’s rank correlation.

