## Methods / design

### Study design

This phase 2a study is designed as a European multicentre 6-month double blind randomized controlled trial (RCT) of AZD0530 versus placebo, followed by a 12 month open-label extension phase.

Eligible subjects are randomized 1:1 to one of two groups: Group 1 will undergo treatment with 100 mg AZD0530 once daily for the entire duration of the trial; group 2 will first be given placebo for the first 6 months before starting AZD0530 for 12 months. After undergoing baseline evaluation, the main outcome criteria and safety endpoints are evaluated at 6, 12 and 18 months after first study drug dosing. In addition, participants are evaluated on safety endpoints 3 weeks after first drug dose/switch to open label phase and after 3, 9 and 15 months. There will be three comparison groups: AZD0530 versus placebo in the 6-month RCT phase (A), placebo group (months 1–6) versus the open label extension phase of the same group (months 7–12) (B) and Open label extension group versus age-, gender-, and demographically-matched historic controls (C).

Figure 1a summarizes the study design and study procedures, Fig. 1b illustrates the comparison groups.

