**Table 1 Tab1:**
[figure not shown]
Schedule of enrollment, intervention, and assessments during study

*RCT* Randomized controlled trial, *CAJIS* Cumulative analogue joint involvement scale, *SF-36* 36-item Short Form Survey, *FOP I-ADL* Fibrodysplasia Ossificans Progressiva Instrumental Activities of Daily Living.

*Telephone/virtual visit unless clinically indicated. ^†^Includes pregnancy test for women of childbearing potential. ^‡^No more than 7 days between baseline PET/CT and start study medication

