#### Secondary endpoints

Secondary endpoints can be divided into several categories:Adverse events: The incidence and severity of adverse events during the different stages of the trial.Imaging endpoints including the change in HO volume and FOP activity on ^18^F NaF PET/CT.Clinical endpoints such as the number of reported flare-ups through daily diary, cumulative analogue joint involvement scale (CAJIS), Range of Motion, and questionnaires Short Form Health Survey-36 (SF-36) and FOP Independent Activity of Daily Living (FOP-IADL).Markers target engagement and efficacy surrogates including bone turn-over biomarkers, AZD0530 pharmacokinetic measurements, and experimental markers.

The outcomes are compared in all three comparison groups.

The endpoints are in line with the agreed Core Outcome Sets by the International Clinical Council on FOP [23]. A detailed description of the endpoints can be found in Additional file 1.

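### Randomised PET comparison tests change in NaF SUV without baseline SUV as a covariate: a minor loss of precision whose size depends on a correlation the article does not give

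*Protocol article*

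**What the plan says.** All references are to the Protocol article.

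- **Analysis.** Under Analyses of secondary endpoints, changes in whole-body "NaF SUV will be measured in comparison groups A and B and compared by t-test (if normally distributed) or by Mann-Whitney U test", the latter if the data are not normally distributed. No baseline covariate is named.
- **Neighbouring endpoints.** The next paragraph says that changes in CAJIS, SF-36, range of motion and FOP I-ADL "will be compared in comparison groups A and B by linear mixed models".
- **Status.** PET activity is secondary. The Secondary endpoints section lists "Imaging endpoints including the change in HO volume and FOP activity on" NaF PET/CT after adverse events.
- **Comparisons.** Under Study design, "Eligible subjects are randomized 1:1 to one of two groups". Comparison A is the 6-month contrast of these arms. Comparison B sets two periods of the placebo group against each other, within patients.
- **Baseline data.** The footnote to Table 1 reads "No more than 7 days between baseline PET/CT and start study medication", so a baseline scan close to first dose is already scheduled. The footnote does not concern the analysis.

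**The concern.** A two-sample test on change scores fixes the coefficient of baseline at exactly 1. In a randomised comparison, the most precise linear use of baseline lets the data estimate that coefficient. With equal variances at the two visits the coefficient equals r, so forcing it to 1 over-corrects whenever r is below 1. If r is below 0.5, the change is noisier even than month-6 SUV taken alone.

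Two things are at stake in a trial this small. The interval for the PET effect may be wider than the collected data allow. In addition, if the arms differ by chance in baseline SUV, part of that difference stays in the estimate. Randomisation is stratified by site only, so the design does not balance baseline activity.

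**Working it through.** **1. The plan's own figure, to fix the numbers per arm.** Sample size calculations states that "progression of HO in FOP is estimated at 120,000 mm^3^ on average per 6-month period with a standard deviation of 48,000 mm^3", with a target difference "or 60,000 mm3, with a standard deviation of 24,000 mm^3" in treated patients. With 8 per arm:

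- Standard error = √(48,000²/8 + 24,000²/8) = √360,000,000 ≈ 18,974.
- Noncentrality = 60,000/18,974 ≈ 3.16, with Satterthwaite df ≈ 10.3.
- Two-sided 5% power = 81.5% (74.7% with 7 per arm), against 80% stated.
- 16/(1 − 0.20) = 20 at the start.

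The figure reproduces. It concerns HO volume; the article gives no power figure for PET. It is used here only to set N = 16 to 20.

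**2. Variance of the two analyses.** Let s² be the SUV variance at each visit (assumed equal) and r the correlation between baseline and month 6.

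- Change score: 2(1 − r)s².
- ANCOVA, large sample: (1 − r²)s².
- Ratio, ANCOVA to change: (1 + r)/2.
- Small-sample cost of estimating the slope: multiply the ratio by 1 + 1/(N − 4), which is 1.083 at N = 16 and 1.063 at N = 20.

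The article gives no r, so it is varied. Information lost by the change score is 1 minus the corrected ratio.

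| r (assumed) | (1+r)/2 | Corrected ratio, N=16 / N=20 | Information lost by change score |
|---|---|---|---|
| 0.3 | 0.65 | 0.704 / 0.691 | 30% / 31% |
| 0.5 | 0.75 | 0.812 / 0.797 | 19% / 20% |
| 0.7 | 0.85 | 0.921 / 0.903 | 8% / 10% |
| 0.8 | 0.90 | 0.975 / 0.956 | 2–3% / 4% |
| 0.9 | 0.95 | 1.029 / 1.009 | none; ANCOVA 3% / 1% worse |

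The methods break even where (1 + r)/2 × [1 + 1/(N − 4)] = 1, that is r = 24/13 − 1 ≈ 0.85 at N = 16 and r = 32/17 − 1 ≈ 0.88 at N = 20. As r approaches 1, ANCOVA's excess variance cannot exceed 1/12 ≈ 8% or 1/16 ≈ 6%, which is about 4% or 3% in the standard error.

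**3. Simulation** (20,000 trials per setting, bivariate normal, pooled t-test on change against ANCOVA, assumed effect of 1 SD of SUV). Power, change vs ANCOVA:

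| r | N=16 | N=20 |
|---|---|---|
| 0.3 | 35% vs 47% | 43% vs 58% |
| 0.5 | 46% vs 54% | 56% vs 66% |
| 0.7 | 67% vs 71% | 78% vs 82% |
| 0.8 | 84% vs 84% | 91% vs 92% |

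With no effect, rejection rates lay between 4.6% and 5.4% for both methods.

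**4. Baseline imbalance.** Given an observed baseline difference d between arms, the change-score difference has null expectation −(1 − r)d. With 8 per arm the SD of d is √(2/8) = 0.5 SD of SUV. An imbalance of that size shifts the result by 0.35 SD at r = 0.3, 0.25 at r = 0.5 and 0.15 at r = 0.7. Under the same linear model, ANCOVA removes the shift.

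**The case against.** The strongest reply is that nothing here is invalid. The change-score comparison is unbiased over randomisations and holds its type I error, and the imbalance in step 4 is already part of that error rate. The endpoint is secondary in a phase 2a trial, with no power claim attached. All of this stands, and it sets the size of the point.

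Several stronger readings are tempting, but the article does not support them:

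- **That the plan ignores baseline SUV.** A change subtracts it. Only the covariate is absent.
- **That SUV fluctuates, so r must be low.** The article calls PET a measure of activity and describes flare-ups, but it gives no repeatability or correlation figure and does not say that whole-body SUV fluctuates. Its Discussion also describes slow progression and marked heterogeneity; stable differences between patients would raise r.
- **That a third of the information is wasted.** In large samples that needs r of about 0.33. It is one point in an assumed range, neither a bound nor a result.
- **That the mixed models for the clinical scores expose an inconsistency.** Those models are also described for changes, and a mixed model on changes need not contain a baseline covariate.

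Two limits of the calculation also stand: it covers neither the Mann-Whitney branch nor skewed SUV, so the gain there is not quantified.

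It might also be said that a short article leaves such detail to the full protocol or analysis plan. That does not remove the point, because the article names the tests and a two-sample test on changes has no place for a covariate.

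**Conclusion.** The point holds as a minor loss of precision in randomised comparison A. At 8 to 10 patients per arm the loss runs from about 30% of the information at r = 0.3 to 2–4% at r = 0.8, and it reverses slightly at r = 0.9. These figures assume normal data, equal variances at the two visits and a linear relation, and r itself is assumed throughout.

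A reader might infer that the planned PET result would be biased or its p-value wrong. It would not be: this is an efficiency matter, and conditional imbalance is the only further drawback. The argument does not extend to comparison B, which is within patients and raises a different question, that of pairing.

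**What to change.** Change one sentence, for comparison A only: analyse month-6 whole-body NaF SUV by ANCOVA with treatment arm and baseline SUV in the model, and report the adjusted difference with its 95% confidence interval. If SUV is clearly non-normal, use a log scale, a rank-based version or a permutation p-value, with the choice fixed in advance. Keep the change from baseline as a descriptive summary by arm.

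No new scans, visits or patients are needed, because baseline PET/CT is already scheduled. The cost is one degree of freedom and, if r turns out to be about 0.9 or higher, a few percent of precision.

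### Comparison B of 18F-NaF SUV change is within-patient, but the plan gives it the same two-sample rule as the randomised comparison; Mann-Whitney U does not fit it, and the t-test is not stated to be paired

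*Protocol article*

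**What the plan says.** Under Study design, the protocol article defines comparison B as "placebo group (months 1–6) versus the open label extension phase of the same group (months 7–12) (B". Comparison A is AZD0530 against placebo in the six-month randomised phase.

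Under Analyses of secondary endpoints, one rule covers the SUV changes in both comparisons: they are "measured in comparison groups A and B and compared by t-test (if normally distributed) or by Mann-Whitney U test (if non-normally distributed". Under Analyses of primary endpoint, the between-arm primary outcome has the same pair of tests: it "will be compared by t-test (if normally distributed) or by Mann-Whitney U test (if non-normally distributed) for statistical significance".

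Other endpoints in comparison B are handled differently in the same section. For "radiographic HO progression across all time points in comparison groups B and C, we will use linear mixed models" is the stated approach, and CAJIS, SF-36, range of motion and FOP I-ADL "will be compared in comparison groups A and B by linear mixed models". SUV change is the exception, and no reason is given.

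**The concern.** In comparison B each patient contributes two changes: baseline to month 6 on placebo, and month 6 to month 12 on open-label AZD0530. They are linked in two ways. They come from the same patient, whose own rate of disease activity may carry through both periods. They also share a scan: the month-6 value closes the first change and opens the second, so its measurement error enters the two with opposite signs.

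A two-sample test treats the two sets of changes as coming from different people. If the pairs are positively correlated, it overstates the standard error of the difference and loses power. If they are negatively correlated, it understates that standard error and rejects too often. At stake is the p-value for one imaging endpoint in the before-and-after comparison, in a trial too small to waste information.

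**Working it through.** **1. Inputs.**
- Randomisation is 1:1 of 20 patients (Study design; Sample size calculations), so about 20/2 = 10 are in the placebo arm. With the planned 20% drop-out, 10 × 0.8 = 8 remain.
- Nominal two-sided alpha is 0.05 (Sample size calculations).
- Scan times: "the main outcome criteria and safety endpoints are evaluated at 6, 12 and 18 months after first study drug dosing", after a baseline evaluation. I take SUV to follow this schedule; the schedule table is not legible in the text at hand, but comparison B needs these scans.
- The correlation ρ between a patient's two SUV changes is not given. I assume a range of −0.5 to +0.5.

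**2. The plan's own figure.** The article gives none for SUV in comparison B. Its sample-size figure is for the primary endpoint, and it reproduces. The standard error is √[(48,000² + 24,000²)/8] = √360,000,000 ≈ 18,974. The non-centrality is 60,000/18,974 ≈ 3.16 on 10.3 Welch degrees of freedom, which gives power of 81.5% against the stated 80%. Also 16/(1 − 0.2) = 20. This supplies n = 8 but does not bear on comparison B.

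**3. Why ρ need not be zero.** Write a patient's SUV at each scan as a level, plus a patient-specific change per period with variance v_b, plus independent scan error with variance v_e. Then:
- Cov(Y6 − Y0, Y12 − Y6) = v_b − v_e
- Var of each change = v_b + 2v_e
- ρ = (v_b − v_e)/(v_b + 2v_e)

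Pure scan error (v_b = 0) gives ρ = −0.5. With v_b = 4v_e, ρ = 3/6 = +0.5. Zero requires v_b = v_e exactly.

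**4. What the unpaired test gets wrong.** With a common variance σ², the mean difference between periods has true variance 2σ²(1 − ρ)/n. The unpaired test uses 2σ²/n. The ratio of true to assumed variance is 1 − ρ: 1.5 at ρ = −0.5 and 0.5 at ρ = +0.5.

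**5. Simulation.** Bivariate normal changes with equal variances were analysed at nominal two-sided 5% (100,000 runs for the t-tests, 20,000 for the exact rank tests). Results for n = 8:

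| ρ | Type I: unpaired t | Type I: Mann-Whitney | Type I: paired t | Type I: signed-rank | Power, 1-SD shift: unpaired t | Power, 1-SD shift: paired t |
|---|---|---|---|---|---|---|
| −0.5 | 10.7% | 10.2% | 4.9% | 3.7% | 47% | 29% |
| −0.3 | 8.2% | 7.8% | 5.1% | 3.9% | 47% | 33% |
| 0 | 4.8% | 4.9% | 4.8% | 3.9% | 46% | 41% |
| +0.3 | 2.3% | 2.3% | 5.0% | 3.8% | 46% | 54% |
| +0.5 | 1.1% | 1.1% | 5.0% | 4.0% | 46% | 68% |

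A second run at n = 8 agreed to within about a point. At ρ = −0.5, type I error was 10.5% (t) and 10.0% (Mann-Whitney), and power was 48% unpaired against 30% paired. At ρ = +0.5, power was 45% against 67%.

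With all 10 patients the pattern is the same. Type I error for unpaired t and Mann-Whitney is 10.6% and 9.5% at ρ = −0.5, and 0.9% and 0.8% at ρ = +0.5. Power at ρ = +0.5 is 59% unpaired against 80% paired.

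**The case against.** Three points count on the other side.

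First, the article writes only t-test, without calling it paired or independent, and where it means a particular two-sample form (the unequal-variance test in the sample-size section) it says so. A paired t-test for B is therefore a possible reading. This stands, and a reader who infers that the plan prescribes an unpaired t-test for B goes further than the text. It does not rescue the non-normal branch, because Mann-Whitney U has no paired form.

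Second, a reader might infer that the p-value for B is certain to be wrong, or that false positives are inflated. The documents support neither. At ρ = 0 the unpaired tests hold their size; under positive correlation they are conservative; and no correlation is given. The figure of about 10% belongs to the limiting case of pure scan error. Nor does pairing always add power: at ρ = −0.5 the paired test has less, because the higher rejection rate of the unpaired test there comes with an invalid size.

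Third, the article condenses a longer protocol, and an analysis plan may name a paired test. That tempers how sure one can be about the analysis that will be run. It does not make this a mere omission: the article names a specific test for a specific comparison, and that test does not fit.

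**Conclusion.** The point holds for comparison B. Mann-Whitney U is the wrong test for a same-patient contrast, and the t-test needs to be stated as paired. If the two-sample tests are run as written, their size is right only if a patient's two changes happen to be uncorrelated. Between ρ = −0.5 and +0.5 at n = 8, the true type I error goes from about 10% to about 1%. The direction cannot be settled from the article. The figures rest on the assumed correlations, normal changes and equal variances in the two periods.

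Severity is minor to moderate. A reader might take this as undermining the trial's efficacy result, but it touches one secondary endpoint in one uncontrolled comparison of about 8 to 10 patients. The two-sample tests suit comparison A, so the randomised SUV result is sound on this point, as are the primary endpoint and the sample size. The article ties no success criterion to the SUV p-value in B.

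**What to change.** Split the SUV sentence by comparison. For A, keep the two-sample t-test or Mann-Whitney U. For B, specify one of these:
- a paired t-test on each patient's difference between the two changes, with the Wilcoxon signed-rank test as its non-parametric counterpart; or
- a linear mixed model with a patient random effect, the class of model already planned for the other endpoints in comparison B.

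If the mixed model is chosen, its covariance should let the two changes correlate in either direction. A random intercept fitted to the change scores alone allows only zero or positive correlation, so it would not cure the inflated error when scan noise dominates.

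The cost is one sentence in the protocol or analysis plan. No new data, visits or patients are needed. The change should be made before SUV data are unblinded.
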